#### Primary Care Access Information

2.5.2

All patients will be asked to provide information regarding the role of their primary care physician in the management of HF. The survey questions regarding primary care access were as follows: (i) Do you know the name of your primary care physician? (ii) Has your primary care physician made any changes to your HF medications? (iii) Did your primary care physician refer you to any specialist because of complaints associated with HF? These survey questions will enable us to obtain real‐world information about the individual and structural determinants of access to primary healthcare and the availability and accessibility of primary healthcare professionals and facilities in Türkiye for patients with HF.

#### Frailty Assessment

2.5.3

The term “frailty” describes a multidimensional syndrome that leads to a loss of reserves, including physical ability, energy, cognition, and health status. Frailty is a poor prognostic factor that affects more than half of patients with HF [18]. Therefore, we integrated the Canadian Study of Health and Aging Clinical Frailty Scale into the TURK‐HF registry to measure the clinical frailty of patients with HF based on clinical judgment [19, 20, 21]. The Clinical Frailty Scale proposed by the Canadian Study of Health and Aging is a seven‐item scale ranging from 1 (indicating robust health) to 7 (indicating complete functional dependence on others) [19]. Frailty was evaluated at the time of study enrollment by a participant physician using the Canadian Study of Health and Aging Clinical Frailty Scale. This approach is closest to the true meaning of frailty, which is defined as a loss of physiological reserve independent of comorbid conditions or reasons for physical limitation, and it considers cognitive deficits [18, 19].

#### HRQoL

2.5.4

HRQoL is defined as an individual's perceived physical and mental health over time, and HF is associated with poor HRQoL [22]. The EQ‐5D‐5L is a widely used generic measure of health status that comprises two components. The first part (the descriptive system) assesses HRQoL in five dimensions, each representing a specific aspect of the patient's HRQoL. The five dimensions are mobility, self‐care, usual activities, pain/discomfort, and anxiety/depression [23]. Each dimension has five response levels (no problems, slight problems, moderate problems, severe problems, and extreme problems/unable). This part of the EQ‐5D‐5L questionnaire provides a descriptive profile that can be used to generate a health state profile. For example, a patient in health state 12345 would have no problems with mobility, slight problems with self‐care (washing or dressing), moderate problems with doing usual activities, severe pain or discomfort, and extreme anxiety or depression (Figure 3A,B). The second part of the questionnaire comprises a visual analog scale, on which the patient rates their perceived health from 0 (representing the worst imaginable health) to 100 (representing the best imaginable health) (Figure 3C). The EQ‐5D‐5L is a valid and reliable instrument for measuring HRQoL and estimating utility values in patients with HFrEF and HFpEF [23, 24, 25, 26, 27]. The TURK‐HF registry was registered with the EuroQol Customer Portal registration number 68900. Accordingly, the EQ‐5D‐5L questionnaire will be administered to patients enrolled in the TURK‐HF registry to determine their HRQoL.

**Figure 3 clc70353-fig-0003:**
[figure not shown]
An example of the Turkish version of the EQ‐5D‐5L descriptive system integrated into the electronic case report form in the TURK‐HF registry (A), an example of the English version of the EQ‐5D‐5L descriptive system (B), and an example of THE EQ visual analog scale (C).

#### HF‐Related Information, Medical History, and Comorbidities

2.5.5

HF‐related information, comprising the New York Heart Association (NYHA) functional classification, type of HF (HFrEF, HFmrEF, HFpEF, or HF with improved ejection fraction), duration of disease (de novo, < 6 months, or ≥ 6 months), previous history of HF‐related hospitalization or unplanned emergency department visits requiring intravenous diuretic treatment, and etiology of HF, will be obtained during the baseline visit. Participants will be questioned about their medical history, including a history of myocardial infarction, revascularization procedures, heart valve surgery, and left ventricular assist device implantation. Comorbidities include atrial fibrillation, peripheral artery disease, cerebrovascular disease, hypertension, dyslipidemia, diabetes, chronic kidney, lung, and liver disease, obstructive sleep apnea syndrome, anemia, thyroid disease, inflammatory connective tissue diseases, previous history of malignancy, and malignancy treatments (surgery and/or chemotherapy and/or radiation therapy), depression, and dementia will also be recorded.

#### Physical Examination, Electrocardiography, Echocardiography, and Laboratory Data

2.5.6

Physical examination findings (systolic and diastolic blood pressure, heart rate, height, and weight) of the registry participants will be assessed during the baseline visit. The patients' body mass index will be calculated automatically using an e‐CRF system. Electrocardiographic data, including heart rhythm (normal sinus rhythm, atrial fibrillation or flutter, pacemaker rhythm, or others), presence and type of bundle branch block, and QRS duration; echocardiographic data, including LVEF, left atrium diameter, mitral E/e' ratio, tricuspid regurgitation velocity, estimated systolic pulmonary artery pressure, tricuspid annular plane systolic excursion, and the presence of valvular abnormalities; and laboratory results, including fasting blood glucose, HbA1c, hemoglobin, serum creatinine, sodium, and potassium, alanine aminotransferase, brain natriuretic peptide or N‐terminal pro‐b‐type natriuretic peptide, thyroid stimulant hormone, uric acid, ferritin, transferrin saturation, cancer antigen 125, and urine albumin‐creatinine ratio, will be registered during the first patient visit. The patient's creatinine clearance will be calculated automatically by the e‐CRF system using the Cockcroft−Gault formula [28].

#### H_2_FPEF Score Calculation

2.5.7

It is critical that scoring systems accurately determine the probability of HFpEF to enable clinicians to decide whether HFpEF is present. The validated H_2_FPEF score utilizes six clinical and echocardiographic parameters to accurately distinguish HFpEF from the non‐cardiac causes of dyspnea [29]. A meta‐analysis reported that a high H_2_FPEF score is associated with an increased risk of HF‐related hospitalization and all‐cause mortality in patients with dyspnea and normal LVEF [30]. However, there are conflicting data regarding the use of scoring systems and their diagnostic utility in the Turkish population [31]. Therefore, we integrated an automatic calculation system into the e‐CRF as a “decision support tool” to calculate the H_2_FPEF score in patients with HFpEF (Figure 4).

**Figure 4 clc70353-fig-0004:**
[figure not shown]
An example of the automatic calculation system integrated into the electronic case report form as a “decision support tool” to calculate the H_2_FPEF score in patients with heart failure with preserved ejection fraction.

#### Medical and Device‐Based HF Therapies

2.5.8

We integrated an assessment algorithm into the e‐CRF to assess the use or non‐use of GDMT by registry participants. Within the scope of this algorithm, the following objectives were identified: first, to determine the treatment classes comprising RAS inhibitors, β‐blockers, MRAs, and SGLT‐2 inhibitors that the participant used; second, in instances where patients were not receiving treatment for HF, the patient and participant physician were asked to provide a rationale for this; third, to ascertain which molecule the participant used (e.g., ramipril for RAS inhibitors, bisoprolol for β‐blockers, eplerenone for MRAs, and dapagliflozin for SGTL‐2 inhibitors); fourth, to identify the daily dosage of each molecule that the participant used; and finally, to determine whether the participant used the target dose of treatment or not (< 50% of target dose, ≥ 50% to < 100% of target dose, or ≥ 100% of target dose) (Figure 5). Other medical treatments, including diuretics (loop, acetazolamide, and thiazide diuretics), ivabradine, glucagon‐like peptide‐1 agonists, digoxin, nitrates, statins, antiplatelet and anticoagulants, ferric carboxymaltose, and a previous history of vaccination, and device‐based HF therapies, including cardiac pacemaker, implantable cardioverter‐defibrillator, or cardiac resynchronization therapy, were also assessed.

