## Introduction

1

Heart failure (HF) is a public health concern associated with higher rates of hospitalization, mortality, and healthcare resource utilization [1]. The incidence of HF in Europe is approximately five per 1000 person‐years in adults, with a prevalence of HF estimated to be between 1% and 2% of the population [2]. However, the prevalence of HF is predicted to rise due to the aging of the population, improved survival rates after myocardial infarction and cancer, advances in pharmacological and device‐based HF therapies, and the greater utilization of heart transplantation over the last decades [1]. Despite these advances, the prognosis of HF remains worse than that of many cancer types, with a 5‐year mortality rate varying from 45% to 60% in adult patients [3].

The proposed terminology based on left ventricular ejection fraction (LVEF) measurement defines “heart failure with reduced ejection fraction” (HFrEF) as LVEF of ≤ 40%, “heart failure with mildly‐reduced ejection fraction” (HFmrEF) as LVEF of 41%–49%, and “heart failure with preserved ejection fraction” (HFpEF) as LVEF ≥ 50% [2]. The main rationale for this terminology is based on clinical trials that have demonstrated beneficial outcomes in patients with HFrEF. Currently, guideline‐directed medical therapies (GDMT), comprising renin‐angiotensin system (RAS) inhibitors, β‐blockers, mineralocorticoid receptor antagonists (MRAs), and sodium−glucose cotransporter‐2 (SGLT‐2) inhibitors, are recommended for patients with HFrEF to reduce the risk of HF hospitalization and death [1, 2]. Notwithstanding compelling evidence from randomized controlled trials and recommendations in current guidelines, the utilization of GDMT among patients with HFrEF remains suboptimal in routine clinical practice [4]. While registry‐based cohort studies have identified numerous patient‐, physician‐, and healthcare system‐related factors associated with the non‐use of GDMT, the discrepancy between current guidelines and clinical practice has not yet been fully elucidated [5, 6].

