In contrast, HFpEF is distinct from HFrEF and represents a heterogeneous clinical syndrome. There is a lack of knowledge regarding the pathophysiological mechanisms, comorbidity burden, and phenotypes of HFpEF [7]. Consequently, our understanding of this complex disease remains limited, and the diagnosis and/or treatment of patients with HFpEF remains a significant challenge. In contrast to patients with HFrEF, treatment options for patients with HFpEF are limited. Historically, numerous randomized clinical trials encompassing RAS inhibitors, β‐blockers, and MRAs have failed to show efficacy in patients with HFpEF [1, 2]. In recent years, several promising studies have been conducted. The results of phase 3 clinical trials with SGLT‐2 inhibitors and finerenone have demonstrated favorable outcomes in patients with HFmrEF and/or HFpEF [8, 9, 10]. However, there are still limited real‐world data on the clinical phenotypes and comorbidity burden in patients with HFpEF and the prognostic impact of these novel treatments.

Acute HF is characterized by the sudden onset of symptoms, either de novo HF or due to the worsening of previously diagnosed HF (WHF) [1, 2]. The term WHF is used to describe the progression of disease in patients with chronic HF that requires hospitalization or unplanned emergency department visits. WHF is recognized as an acute deterioration phase in the natural course of the disease, indicating poor prognosis [11]. Despite its clinical importance, WHF remains inadequately defined, and its management remains challenging. Current WHF data are obtained from randomized controlled trials with a highly selected HF population. Although the prognostic significance of WHF events during the course of the disease is known, there is a paucity of data on the definition, management, and outcomes of WHF in real‐world patients.

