**Figure 5 clc70353-fig-0005:**
[figure not shown]
“Treatment assessment algorithm” integrated into the electronic case report form to determine the use or non‐use of guideline‐directed medical therapies by registry participants. Step‐1: Determine the evidence‐based medication classes* (RAS inhibitors, β‐blockers, MRAs, and SGLT‐2 inhibitors) used by the registry participants. Step‐2: In instances where patients were not receiving treatment for HF, the patient and participant physician were asked to provide a rationale** (e.g., symptomatic hypotension for RAS inhibitors, bradycardia for β‐blockers, hyperkalemia for MRAs, or urinary tract infections for SGLT‐2 inhibitors). Step‐3: In instances where patients were receiving treatment for HF, determine the molecule that the participant used*** (e.g., ramipril for RAS inhibitors, bisoprolol for β‐blockers, eplerenone for MRAs, and dapagliflozin for SGTL‐2 inhibitors). Step‐4: Determine the daily dosage of medication that the participant used (e.g., ramipril 2.5 mg once daily, bisoprolol 10 mg once daily, eplerenone 25 mg once daily, and dapagliflozin 10 mg once daily). Step‐5: Determine whether the participant used the target dose of treatment or not# (< 50% of target dose, ≥ 50% to < 100% of target dose, or ≥ 100% of target dose).

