Suboptimal implementation of evidence‐based HF treatment, particularly in HFrEF, has been documented in various registries [4, 5, 6, 39, 40]. While most reports have been predominantly descriptive, detailing the percentage usage of fundamental HF medications, they often lack comprehensive information on diagnostic methodologies and additional pertinent medications, devices, and interventions. Well‐structured registries have the potential to collect extensive descriptive data and analyze and quantify the underlying causes of inadequate implementation. This can facilitate the identification of specific patient groups with the most significant unmet needs or areas requiring improvement, thereby enabling targeted initiatives to enhance the implementation. The TURK‐HF registry will provide detailed real‐world data on the management strategies used for patients with HF. For this purpose, we created a unique algorithm and integrated it into the e‐CRF as a “work‐up tool” for the first time in Türkiye. This approach included five consecutive questions about the use or non‐use of GDMT in HF. As outlined in the methods section, we questioned the use of treatment classes and scrutinized the specific molecule prescribed and its daily dosage for each category of evidence‐based HF medication. In this way, we will assess the use or nonuse of the target dose or the maximally tolerated dose of HF medications in patients with HF. Furthermore, we examined the justification for the absence of GDMT utilization, considering factors such as contraindications, intolerability, and clinical inertia. Analyzing the real‐world factors and obstacles hindering the effective implementation of GDMT through the TURK‐HF registry offers a unique opportunity to address these challenges in Türkiye.

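### The treatment algorithm asks for a reason only when a drug class is not taken, so it cannot deliver the promised assessment of maximally tolerated dose or explain under-dosing

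*Protocol article*

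**What the plan says.** Section 2.5.8 and the legend of Figure 5 describe the same five steps for RAS inhibitors, beta-blockers, MRAs and SGLT-2 inhibitors. After the class has been recorded, the second step applies to patients without the treatment: "in instances where patients were not receiving treatment for HF, the patient and participant physician were asked to provide a rationale for this". Treated patients take the other branch: "In instances where patients were receiving treatment for HF, determine the molecule that the participant used", followed by the daily dose. The last step is "Determine whether the participant used the target dose of treatment or not", with three possible answers: "< 50% of target dose, ≥ 50% to < 100% of target dose, or ≥ 100% of target dose".

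The Discussion (section 3) summarises class, molecule and daily dose, and presents the result of recording them as follows: "we will assess the use or nonuse of the target dose or the maximally tolerated dose of HF medications in patients with HF". Where it turns to reasons, it links them to non-use: "we examined the justification for the absence of GDMT utilization, considering factors such as contraindications, intolerability, and clinical inertia". Research question (v), in the same section, is wider. It covers patient, physician and health-system barriers to suboptimal use of evidence-based therapy, and the prognostic impact of that use.

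**The concern.** Suboptimal use includes drugs that are taken but under-dosed. The three target-dose bands show that the registry itself treats dose as part of the question. Yet the described steps ask why only when the drug is absent.

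A percentage of target says how far a dose falls short, not whether more could have been tolerated. For a treated patient below target, one explanation points to the patient's tolerance and the other to clinical inertia. These are the kinds of barrier that question (v) sets out to separate. If they are recorded alike, the registry can describe under-dosing but not explain it. A comparison of outcomes by dose band would also mix patients who could not take more, who may be sicker, with patients who were never offered more.

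**Working it through.** The article attaches no figure to this point, so the check sets the described data against the promised output.

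**1. What the steps yield.** Take two patients on the same molecule at the same daily dose, both below target. Patient A is at the highest dose tolerated. Patient B has never been up-titrated.

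| Step (section 2.5.8, Figure 5 legend) | Patient A | Patient B |
|---|---|---|
| 1. Class used | yes | yes |
| 2. Reason for not receiving | not asked | not asked |
| 3. Molecule | same | same |
| 4. Daily dose | same | same |
| 5. Band of target dose | same band | same band |

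The two algorithm records are identical.

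**2. What this does to the promised measure.** For one class, let p be the share of treated patients at or above 100% of target. Let m be the share of treated patients who are below target but at their maximally tolerated dose. The Discussion promises the share at target or maximally tolerated dose, which is p + m. Step 5 identifies p. Nothing identifies m, which can lie anywhere from 0 to 1 − p. The promised share is therefore known only to lie between p and 1, an interval of width 1 − p, which is the whole below-target group. The article gives no value for p, so the width cannot be put as a number.

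**3. Whether other recorded data fill the gap.** Section 2.5.6 records blood pressure, heart rate, potassium and creatinine. Section 2.6 records HF therapies and medication changes every six months. These could hint at intolerance, and patients A and B might differ on them. They do not show whether up-titration was tried before enrolment, or what the physician judged the limit to be.

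**4. What remains answerable.** Reasons for non-use are sought from both patient and physician. The legend's examples are specific to each class, which supports reading Step 2 class by class. Barriers to non-use, the distribution of dose bands, and outcome by dose band can all be reported from the data as described.

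**The case against.** **Figure 5 is not shown.** The legend carries footnote marks on the rationale and target-dose steps, and the text behind them is absent. The e-CRF may hold options that the article does not print. This stands as a caveat. Against it, both written accounts place the rationale on the non-receipt branch, and the Discussion derives its dose assessment from class, molecule and dose.

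**A condensed article may leave detail to the full protocol or analysis plan.** That is true of denominators and models. Here, a stated set of questions does not support a stated output. If the reason was not recorded, no analysis plan can recover it.

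**Question (v) is broader than dosing.** This stands. A reader might infer that the gap defeats the barriers question as a whole. It does not: it affects barriers to adequate dosing among treated patients, which is part of one of six research questions.

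**Ejection fraction.** A reader might also infer that non-use is counted as suboptimal whatever the ejection fraction. The Introduction says the four classes "are recommended for patients with HFrEF to reduce the risk of HF hospitalization and death" and that trials of three of them "have failed to show efficacy in patients with HFpEF", while the algorithm is described for participants generally. The document does not support that inference. It defines no non-use score and does not say that non-use will be pooled across ejection-fraction groups. HF type (section 2.5.5) and LVEF (section 2.5.6) are recorded, so use can be tabulated by group. The reasons named are examples, so the absence of a not-indicated option cannot be concluded. Recording all classes in all groups also has a purpose, since the Introduction reports favourable newer results outside HFrEF and calls for real-world data.

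**Conclusion.** The point holds in a limited form. As described, the algorithm cannot distinguish a maximally tolerated dose from a lack of up-titration, so the assessment promised in the Discussion cannot be made and barriers to adequate dosing cannot be answered. Barriers to non-use are unaffected.

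The gap covers all treated patients below 100% of target for a given class. How many that is cannot be derived from the article, and any percentage would be an assumption. Section 2.8 reports 1240 patients registered within the first six months and plans baseline results after one year of enrolment, so the number without a baseline value grows as enrolment continues.

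The conclusion assumes that the e-CRF matches the five steps as written, and that the unseen figure and footnotes add no reason or tolerability field for treated patients.

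**What to change.** First check the live e-CRF. If it already has such a field, the article needs only to describe it.

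If not, add one conditional item for each class taken below 100% of target, with two parts:
- whether the physician considers the current dose to be the maximally tolerated one;
- why it is below target, using the Step 2 reasons plus two further options, titration ongoing and no attempt made.

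For patients already enrolled, collect the item from the next six-monthly visit, where section 2.6 already provides for an assessment of HF therapies. Store the answer as a value for that visit and do not carry it back to baseline, because dose and tolerance may have changed.

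The alternative is to withdraw the maximally-tolerated-dose statement from the Discussion and limit question (v) to non-use and dose bands.

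The first option costs slightly longer data entry and leaves no baseline value for patients enrolled so far. The second costs only wording but gives up the explanation of under-dosing. Either way, the change concerns what is recorded or claimed and implies no dose or treatment rule.
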